## Abstract

**Introduction::**

Slow-release oral morphine (SROM) was introduced as an alternative form of opioid agonist treatment (OAT) in British Columbia (BC), Canada in 2017. While clinical guidelines in BC recommend SROM based on expert consensus and experience, there is limited real-world evidence on populations most likely to benefit from SROM compared to other forms of OAT, particularly in the context of widespread fentanyl exposure. We will estimate the comparative effectiveness of SROM versus methadone and buprenorphine/naloxone on OAT discontinuation and all-cause mortality among key sub-populations in BC.

**Methods::**

We will conduct a population-level retrospective cohort study using linked data from nine provincial health administrative databases. The study population includes adults (≥18 years) in BC who initiated SROM, methadone, or buprenorphine/naloxone between June 1, 2017, and December 31, 2022. Key sub-populations will include incident users with no prior OAT history and prevalent new users with prior OAT experience stratified by OAT type, stability, and medication switching history. The primary outcomes are time to OAT discontinuation and all-cause mortality, while overdose-related acute care visits will be examined as a secondary outcome. To estimate both the initiator effect and the effect of treatment at guideline-recommended doses, we will apply marginal structural models using inverse probability treatment weighting and ‘clone-censor-weights’ approach to address confounding by indication and time-varying confounding. Sensitivity analyses will evaluate the robustness of our findings, including cohort and timeline restrictions, alternative outcome definitions, and alternative estimation strategies including high-dimensional propensity score and instrumental variable approaches.

**Discussion::**

This study will generate real-world evidence on the comparative effectiveness of SROM versus methadone and buprenorphine/naloxone across clinically distinct OAT sub-populations. The findings will support evidence-informed updates to OAT guidelines and clinical decision-making in BC and other jurisdictions facing escalating opioid-related harms.

## Introduction

### Slow-release oral morphine as an alternative OAT

Methadone and buprenorphine/naloxone are common pharmacological treatments for opioid use disorder (OUD) aimed at reducing unregulated opioid use, overdose risk, and associated harms.[1–10] However, not all individuals respond well to these treatments, necessitating alternative options such as slow-release oral morphine (SROM), extended-release naltrexone, extended-release buprenorphine, and injectable opioid agonist therapies.[6,8,11] Methadone, a full mu-opioid receptor agonist, has long been the gold standard for OAT due to its high retention rates but requires careful dose titration due to its long half-life, overdose risk, and potential for QT (a measure of the heart’s electrical cycle on electrocardiogram) prolongation.[12] Buprenorphine/naloxone, a partial agonist, has a better safety profile but exhibits a ceiling effect on opioid receptor activation, which may limit its efficacy for individuals with high opioid tolerance.[6]

In contrast, SROM is a full agonist with a long-acting formulation which provides stable plasma levels with once-daily dosing without a ceiling on its opioid effects, making it a potential alternative to methadone and buprenorphine/naloxone. Additionally, unlike methadone, SROM does not prolong the QT interval and may have a lower risk of sedation.[13–15] Originally developed for pain management, SROM has gained recognition as an opioid agonist treatment (OAT) in several countries, including Austria, Germany, and Canada, though its regulatory approval status varies. SROM, marketed as Kadian^®^, a 24-hour extended-release morphine capsule, was introduced in 2017 under British Columbia, Canada’s (BC) provincial drug plan (PharmaCare) as an off-label option for individuals who have not found success with methadone or buprenorphine/naloxone, though it is unclear who are most likely to benefit.[5,6]

### Adapting clinical guidelines to a new drug landscape

Clinical guidelines in BC had previously regarded SROM as a third-line treatment behind buprenorphine/naloxone and methadone but updated their guidance in 2023, in response to rising overdose death rates across the province, to remove the tiers and advise collaborative treatment selection based on client preferences, clinical judgement and contextual circumstances.[6] Guidance for SROM is largely based on clinical consensus and expert opinion due to overall limited evidence to support decision-making.[6] This client-centered shift acknowledges that prior experiences with OAT often shape future treatment decisions. SROM may be an alternative option for individuals who have experienced negative outcomes with other OAT medications, such as incomplete elimination of withdrawal with buprenorphine/naloxone, or intolerable side effects with methadone, including sedation, emotional blunting, or cardiac risks such as QT prolongation.[11] Individuals with contraindications to methadone, including ventricular arrhythmias or concurrent use of QT-prolonging medications, may particularly benefit from SROM as the medication does not affect the QT interval.[11] Moreover, frequent or early switching between OAT options is often a signal of suboptimal treatment fit, whether due to poor tolerability, inadequate therapeutic response, or individual treatment goals not being met.[6,11]

While the 2023 BC guideline outlined expert-informed protocols for switching from methadone or buprenorphine to SROM, these recommendations are not supported by empirical evidence, and the comparative effectiveness of this form of OAT remains uncertain. Moreover, the unregulated drug supply in BC has been increasingly contaminated with fentanyl, a synthetic opioid 40–100 times more potent than heroin. By 2017, fentanyl was detected in over 80% of unregulated drug deaths in the province.[16] People who use fentanyl may have higher tolerance and require higher doses to maintain OAT compared to those using prescription opioids, highlighting the urgent need for tailored treatment approaches.[17] This shift challenges existing OAT guidelines as they are based on evidence established before fentanyl was a dominant drug in the unregulated supply. Given fentanyl’s increasing prevalence and role in rising overdose risks, it is critical that we have an understanding of the comparative effectiveness and best practices for every OAT option in fentanyl-tolerant individuals.

### Evidence on SROM’s effectiveness and safety

Some studies suggest that SROM offers comparable retention rates to methadone, with potential advantages in reducing heroin cravings, improving mental health outcomes, and increasing individual’s treatment satisfaction.[18–21] However, others raised concerns regarding shortage of evidence, misuse, and lack of standardized guidelines.[6,22] A 2010 systematic review and a 2013 Cochrane review found that SROM was comparable to methadone in retention rates and withdrawal symptom relief, with potential benefits in reducing depression and cravings.[18,19] However, the former reviewed 13 studies involving a total of 750 individuals, of which only one was a randomized controlled trial (RCT) with 64 participants followed for 7 weeks, while eight studies lacked a comparison group.[18] The Cochrane review included only three RCTs with a total of 195 participants, of which two were short-duration crossover trials lasting 6 and 7 weeks, and none enrolled individuals with documented poor response to other maintenance treatments.[19] A 2019 meta-analysis of four RCTs (including the same three studies from the 2013 Cochrane review) reinforced these findings, indicating SROM’s equivalence to methadone in retention and heroin use reduction.[23] However, all participants were recruited from European settings before 2010 and were stabilized on OAT, limiting generalizability to more clinically complex populations.

Another meta-analysis was conducted in 2022 to investigate the effectiveness of different OAT medications, and SROM was only featured in 4 of 79 RCTs.[24] As a result, the authors could not draw conclusions regarding SROM’s comparative effectiveness on treatment retention due to limited high-quality trials. Notably, only 6 distinct RCTs that compare SROM to another OAT medication were included among these systematic reviews and meta-analyses, with the most recent trial conducted over 10 years ago. None of these RCTs were conducted among people who use illicit fentanyl or had indicated a poor response to another OAT medication prior to the trial with SROM,[23,24] and only one trial compared SROM with buprenorphine.[25]

More recently, the pRESTO trial in Vancouver (2021) aimed to evaluate SROM’s effectiveness compared to methadone in fentanyl-exposed populations but was terminated early due to COVID-19, leaving significant gaps in understanding its long-term retention and safety in high-risk patients.[26,27] Observational studies conducted in Germany in 2016 and 2017 showed successful transitions from methadone and buprenorphine to SROM,[28] 60.6% retention at 1 year, reduction in heroin and intravenous drug use, and important improvements in mental and physical health among patients with extensive, but often unsatisfactory prior OAT experience.[29] Additionally, a 2021 hospital-based study in Canada found the ability to offer SROM, in addition to methadone and buprenorphine, resulted in increased rates of OAT initiation among hospitalized patients with OUD, high post-discharge retention, and that patients with chronic pain were more likely to initiate with SROM.[30] However, these studies were limited by small sample sizes[30] and did not compare long-term SROM retention to methadone or buprenorphine.[29,30]

Concerns regarding SROM’s safety have raised questions about its role in OAT. A 2016 epidemiological study in France reported high rates of SROM use by injection, and illegal acquisition, indicating significant risks of misuse and diversion.[31] Also in France, a 2020 population-based cohort study (using data from 2012–2014) found that SROM users had 3.8-fold and 2-fold higher overdose incidence and 9.1-fold and 3.9-fold higher mortality incidence compared to buprenorphine and methadone, respectively, along with increased bacterial infections. However, a relatively small cohort of SROM users had more comorbidities such as mental health and alcohol use disorders but were prescribed benzodiazepines less than methadone or buprenorphine users, indicating less comprehensive care than those receiving these conventional treatments and potential selection bias.[32] Nonetheless, evaluating the real-world effectiveness of SROM as second-line treatment, compared to methadone and buprenorphine/naloxone, among key sub-populations and determining who will benefit most from this form of OAT remains a pressing public health concern amid the ongoing overdose crisis.[22,33]

### Impact of COVID-19 on OAT policies and outcomes

The COVID-19 pandemic necessitated substantial changes in OAT delivery to ensure continued care while minimizing in-person interactions. Across multiple jurisdictions, including Canada,[34,35] the U.S.,[36,37] Australia,[38] New Zealand,[39] and the United Kingdom,[40] regulatory changes were implemented to expand take-home dosing, integrate telehealth consultations, and ease urine drug testing requirements. These policy shifts broadened OAT accessibility, particularly for individuals facing barriers to in-person daily treatment.[35] A survey-based study from Ontario involving 402 patients and 100 prescribers found that expanded unsupervised dosing during COVID-19 was not associated with increased rates of overdose, emergency department visits, or hospitalizations, although diversion behaviors such as dose sharing and trading were more frequently reported.[35] While these adaptations largely applied to methadone and buprenorphine/naloxone, the impact on SROM accessibility and treatment outcomes remains unclear.[34] Interviews with 25 opioid treatment program directors in the U.S. revealed mostly positive responses to COVID-related regulatory changes, though some raised concerns about reduced clinical oversight, medication diversion, and patient isolation.[41] Additionally, while 37 U.S. states initially adopted expanded methadone take-home flexibilities, four states later rescinded these changes, reverting to pre-pandemic regulations.[37] These findings highlight the variability in policy implementation across jurisdictions and raise questions about the long-term sustainability of these regulatory adaptations.

BC operates within a single-payer healthcare system where access to OAT is not restricted by site type or insurance status. Unlike the U.S., where OAT coverage often depends on Medicaid expansion and site-specific regulations (e.g., methadone often limited to certified clinics), BC allows OAT delivery in diverse clinical settings and provides a wider range of medications, including SROM. This unique regulatory landscape provides a rare opportunity to generate real-world evidence on SROM’s effectiveness relative to methadone and buprenorphine/naloxone using the population-based linked administrative dataset in BC.

### Objective

Our objective is to conduct a population-level retrospective observational study using nine linked provincial administrative databases to compare the effectiveness of SROM versus methadone and buprenorphine/naloxone in BC from 2017 to 2022 among key sub-populations. We will evaluate both the initiator effect (treatment outcomes based on initial OAT dispensation) and the per-protocol effect (treatment outcomes when adhering to the initial OAT regimen, according to BC clinical guidelines) on treatment discontinuation and all-cause mortality in real-world settings.

## Materials and Methods

### Study design

This study is designed as a population-based retrospective cohort study, aiming to emulate a suite of target trials (i.e., hypothetical randomized clinical trials, RCTs) for individuals initiating methadone, buprenorphine/naloxone, or SROM between June 1, 2017, and December 31, 2022, in BC, Canada. This timeline ensures the availability of SROM alongside methadone and buprenorphine/naloxone in BC. Although RCTs are the gold standard for determining comparative effectiveness, they are often time-intensive and may lack generalizability to broader population.[42] By leveraging large-scale health administrative datasets and advanced statistical techniques, observational studies can address many common biases and yield treatment effect estimates based on real-world evidence.[43–46] We will explore the effect variation across key sub-populations which will help identify most beneficiary group from SROM compared to methadone, buprenorphine/naloxone. Key elements of the target trials and their emulations are summarized in Table 1.

This study will utilize population-level data derived from the linkage of nine provincial health administrative databases in BC, where residents are required to participate in a single-payer health insurance system. Using the BC PharmaNet database,[47] which captures daily medication dispensations, we will identify dispensation dates and doses for methadone, buprenorphine/naloxone, and SROM (refer to **S1 Table** for a list of drug/product identification numbers) to define treatment episode. Additional databases include the Discharge Abstract Database[48] (DAD, documenting hospitalizations), Medical Services Plan[49] (MSP, containing physician billing records), BC Vital Statistics [50] (BCVS, capturing deaths and underlying causes), BC Provincial Corrections [51] (recording incarceration entries and releases), Perinatal Care Database[52] (PSBC, covering maternal and infant outcomes), National Ambulatory Care Reporting System[53] (NACRS, documenting Emergency Department visits), Client Roster[54] (providing demographic and geographic data), and the BC Social Development and Poverty Reduction database[55] (tracking social assistance). These datasets are linked at the individual level using a de-identified personal health number assigned by the BC Ministry of Health.[56] A description of these databases and the timeline for data extraction is detailed in **S2 Table**.

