### Study population

We will consider ten sub-populations, based on their prior experience with OAT, in the target trial emulations to identify people who achieve better outcomes from SROM compared to methadone and buprenorphine/naloxone. In each case, the study population will include adults (≥18 years) and exclude those who are pregnant or incarcerated at OAT initiation, and individuals with a history of cancer or palliative care. OAT episodes will be defined as continuous treatment with no gaps exceeding four days for methadone and SROM or five days for buprenorphine/naloxone (see Fig. 1 for details).

These thresholds align with BC guidelines recommending re-titration after these durations.[6] Key sub-populations include (i) incident users – no history of OAT dispensation dating back to January 1, 1996, (ii) prevalent new users – no dispensation for ≥5 days of methadone and SROM and ≥6 days for buprenorphine/naloxone, intended to capture repeated treatment attempts. (iii) prevalent new users – a history of methadone dispensation within past year of the index OAT episode. (iv) prevalent new users – a history of buprenorphine/naloxone dispensation within past year of the index OAT episode, (v) prevalent new users – a history of methadone and buprenorphine/naloxone dispensation within past two years of the index OAT episode, (vi) prevalent new users – completed methadone induction within past two year of the index OAT episode. Induction completion is defined as no dose change within at least two consecutive weeks, (vii) prevalent new users – completed buprenorphine/naloxone induction within past two year of the index OAT episode, (viii) prevalent new users – completed methadone and buprenorphine/naloxone induction during past five years of the index OAT episode, (ix) prevalent new users – individuals initiated treatment with buprenorphine/naloxone, (x) prevalent new users – individuals initiated treatment with methadone (see Table 2 for details).

Pregnant and incarcerated individuals will be excluded since pregnancy requires unique clinical management for treatment interruptions,[6] and incarceration involves distinct treatment protocols.[57]

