### Subgroup and sensitivity analyses

We will conduct a range of sensitivity analyses by restricting the study population and timeline to pre-COVID era, redefining key variables, and applying alternative estimation methods including hdPS estimation, IV estimation (see Table 5 for details).

Because fentanyl had already become the dominant opioid in the drug supply by 2017, it will not be feasible to examinae the effect of pre-fentanyl era on our findings. Relevant findings from each analytical approach will be presented in a forest plot. Any deviations from this protocol will be documented in the final reports.

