## Figures and Tables

**Fig 1. F1:**
[figure not shown]
Construction of treatment episode for opioid agonist treatment for comparing slow-release oral morphine versus methadone and buprenorphine/naloxone

**Table 1: T1:** Key components of the emulated target trials on comparing the initiation of SROM versus methadone and buprenorphine/naloxone to treat people with opioid use disorder using the observational data

Protocol components	Hypothetical target trial	Emulation of the trial from BC health administrative data
Eligibility criteria	Adults aged 18 years or older who initiated OAT with MET, BNX, or SROM between June 1, 2017, and December 31, 2022. Individuals must not be pregnant or incarcerated and have no history of cancer or palliative care.	The same. To identify people who achieve better outcomes from SROM compared to MET and BNX, we will construct ten study populations to emulate the target trials (see Table 2 for details).
Treatment strategies	*For the study population (i) to (viii)* ITT: Initiating OAT with (1) MET, (2) BNX, and (3) SROM. PP: Receipt of at least 1 dispensation of optimal doses*: week 1: MET (≤40mg), BNX (≤16mg/4mg), SROM (≤240mg); weeks 2 through 3: MET (≥30 mg), BNX (≥12mg/3mg), SROM ((≥140mg); week 4 and beyond: MET (≥80mg), BNX (≥16 mg/4 mg), SROM (≥480 mg)[6] *For the study population (ix)* (1) Switching to SROM within 30 days of BNX initiation, (2) Staying on BNX. *For the study population (x)* (1) Switching to SROM within 30 days of MET initiation, (2) Staying on MET.	*For the study population (i) to (viii)* Treatment initiator effect and PP effect of the same strategies as proposed in the target trials. *For the study population (ix) and (x)* Same strategies as defined in the target trials.
Assignment procedures	Randomization. Prescribers, healthcare teams, and individuals are aware of the treatment status.	Individuals will be classified into treatment strategies based on dispensation records. Prescribers, healthcare teams, and individuals are aware of the treatment status.
Time zero	Date of randomization	Date of first OAT dispensation
Outcomes	Time to OAT discontinuation, along with the time to all-cause mortality and overdose-related acute care visit as the secondary outcomes.	Same.

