Follow-up	Intention-to-treat (ITT): from time zero to outcome, death, loss to follow-up, 24 months after time zero, or December 31, 2022, whichever occurs first. Per-protocol (PP): additionally, we will assess adherence weekly and censor follow-up at protocol violation (see Table 3).	Same.
Causal contrasts	ITT for the sub-populations (i) to (viii) and PP for all.	Treatment initiator analysis for the sub-populations (i) to (viii), and PP for all.
Analysis plan	ITT: Hazard ratios will be estimated using Cox PH model. To obtain risk curves and risk differences at 24 months, we will estimate the baseline hazard and combine it with covariate effects to compute cumulative risks. To adjust for potential selection bias due to loss to follow-up, we will use inverse probability weighting (IPW) as a function of baseline and time-varying covariates. PP analysis: same except that individual are censored at non-adherence and uncensored individuals are assigned IPW that are a function of baseline and time-varying variables.	*For the study population (i) to (viii)* Initiator analysis: Marginal structural models with treatment weights from propensity scores models and censoring weights due to loss to follow-up. Weights will be estimated as a function of baseline and time-varying covariates. PP: Same as initiator analysis except potential pre- and post-baseline confounders that are associated with adherence to the treatment strategies will be included in the censoring models. *For the study population (ix) to (x)* Same PP analysis as applied to the study population (i) to (viii), except that individuals’ clone are used with a modified censoring mechanism (see Table 3).

* The optimal SROM doses are determined applying 1:6 MET-to-SROM conversion rate as per BC guidelines.[6]

**Table 2: T2:** Target study populations for comparative effectiveness analysis

Study population	Definition	Rationale
Incident users	(i) No history of OAT dispensation, dating back to January 1, 1996	To evaluate treatment outcomes among individuals initiating OAT for the first time
Prevalent new users	(ii) No dispensation for ≥5 days of methadone and SROM and ≥6 days for buprenorphine/naloxone	To capture repeated OAT attempts after a washout period, reflecting common real-world patterns.

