Prevalent new users with past OAT experience	(iii) A history of methadone dispensation within past year of the index OAT episode	To assess individuals with recent prior experience of specific OAT which may influence current treatment response.
	(iv) A history of buprenorphine/naloxone dispensation within past year of the index OAT episode	
	(v) A history of methadone and buprenorphine/naloxone dispensation in past two years of the index OAT episode	
Prevalent new users who had previously completed OAT induction*	(vi) Completed methadone induction within past two year of the index OAT episode	To assess individuals recently stabilized on methadone and buprenorphine/naloxone, which may influence response to new treatment.
	(vii) Completed buprenorphine/naloxone induction within past two year of the index OAT episode	
	(viii) Completed methadone and buprenorphine/naloxone induction in past five years of the index OAT episode	A history of completing both inductions may reflect complex needs or higher tolerance, informing comparative effectiveness.
Individuals initiated treatment with buprenorphine/naloxone	(ix) Individuals initiated OAT with buprenorphine/naloxone will be included. Switching to SROM within 30 days of initiation will be compared with staying on buprenorphine/naloxone in a two-arm study.	Early switching within buprenorphine/naloxone episode may indicate suboptimal response or poor tolerability.
Individuals initiated treatment with methadone	(x) Individuals initiated OAT with methadone will be included. Switching to SROM within 30 days of initiation will be compared with staying on methadone in a two-arm study.	Early switching within methadone episode likely reflects adverse effects such as sedation, emotional blunting, or QT-related cardiac risk.

* Induction completion is defined as no dose change within at least two consecutive weeks.

**Table 3. T3:** Censoring indication in the primary and secondary analyses for comparing slow-release oral morphine versus methadone and buprenorphine/naloxone.

	OAT discontinuation		All-cause mortality		Overdose-related acute-care visits	
	Initiator	Per protocol	Initiator	Per protocol	Initiator	Per protocol
OAT discontinuation	outcome	outcome				
End of study ^a^	C_1_	C_1_	C_1_	C_1_	C_1_	C_1_
Death	C_2_	C_2_	outcome	outcome	C_2_	C_2_
Loss to follow-up	C_2_	C_2_	C_2_	C_2_	C_2_	C_2_
Deviation from inclusion/exclusion criteria		C_2_		C_2_		C_2_
Deviation from the protocol		C_3_		C_3_		C_3_

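### The Study design section expects to identify the group that benefits most from SROM, but every planned estimate is a within-population contrast, so no between-group statement would be supported

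*Protocol article*

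**What the plan says.** The Study design section gives the purpose of the sub-populations as a search for effect variation: "We will explore the effect variation across key sub-populations which will help identify most beneficiary group from SROM". The Study population section introduces them with "We will consider ten sub-populations, based on their prior experience with OAT" and gives their purpose as "to identify people who achieve better outcomes from SROM compared to methadone and buprenorphine/naloxone". Table 1 treats each as its own emulation: "we will construct ten study populations to emulate the target trials".

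Table 2 defines them. Sub-population (ii) is the broad washout group: "No dispensation for ≥5 days of methadone and SROM and ≥6 days for buprenorphine/naloxone". Sub-populations (iii) to (viii) are prevalent new users restricted by history, for example (iii), "A history of methadone dispensation within past year of the index OAT episode", and (v), "A history of methadone and buprenorphine/naloxone dispensation in past two years of the index OAT episode". Sub-populations (ix) and (x) compare switching to SROM within 30 days with staying on the initial drug, and Table 1 gives them a per-protocol contrast only.

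The Statistical analysis, Initiator analysis and Per-protocol analysis sections describe hazard ratios, 24-month risk differences and risk curves by drug. Sandwich intervals are planned for hazard ratios, and 500 bootstrap samples for risk differences and curves.

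**The concern.** To say which group benefits most is to say that the SROM effect is larger in one group than in another. That needs a difference (or ratio) of effects with its own interval, and the protocol describes none: no interaction term, heterogeneity measure, between-population difference or joint covariance.

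A reader of the results would have only a set of separate intervals. One interval that excludes no effect beside another that does not is not evidence that the effects differ. Nor is the largest point estimate evidence of the largest effect. The Discussion says the findings will inform refinement of treatment guidelines, so a loosely supported statement about who benefits most could be taken further than the data allow.

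**Working it through.** The protocol article gives no sample size, event count or power, so there is no figure of its own to reproduce. The check is a count of planned quantities, a look at the overlap, and three illustrations with stated assumptions.

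**1. What is estimated.** Inputs: eight sub-populations with an initiator analysis and ten with a per-protocol analysis (Table 1); two comparators; two outcomes named as primary under Key measures.
- Initiator: 8 × 2 × 2 = 32 estimates.
- Per-protocol: 8 × 2 × 2 + 2 × 1 × 2 = 36 estimates.
- Total 68, all within one sub-population.
- Possible pairs among (i) to (viii): 8 × 7 / 2 = 28 per comparator and outcome, so 28 × 2 × 2 = 112 for the initiator analysis. Number named in the protocol: 0.

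**2. Overlap, from Table 2.** (iii) to (viii) are largely restrictions of (ii). Anyone in both (iii) and (iv) has had both drugs within one year, hence within two, and so is in (v). Anyone in both (vi) and (vii) is in (viii). Incident users (i) cannot be in (iii) to (viii) with the same episode.

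**3. Standard error of a nested difference.** Let a subset hold a share f of its parent's events, and set the parent's variance to 1, so the subset's variance is about 1/f.
- Correct variance of (subset − parent): 1/f − 1.
- Variance if wrongly taken as independent: 1/f + 1.
- Ratio of standard errors: √[(1 + f)/(1 − f)].

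| f (assumed) | Correct SE | SE if taken as independent | Ratio |
|---|---|---|---|
| 0.2 | 2.000 | 2.449 | 1.22 |
| 0.3 | 1.528 | 2.082 | 1.36 |
| 0.5 | 1.000 | 1.732 | 1.73 |
| 0.7 | 0.655 | 1.558 | 2.38 |

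The separate intervals therefore give the wrong uncertainty for a difference, and the error is towards too much uncertainty.

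**4. Spread under one common effect.** In a simulation of 200,000 draws, eight estimates shared the same true effect, with equal standard errors and equal pairwise correlation (assumed). The gap between the highest and the lowest averaged 2.84 SE at correlation 0, 2.38 at 0.3, 2.01 at 0.5 and 1.56 at 0.7. An unadjusted test of highest against lowest, using the correct standard error, exceeded 1.96 in about 51% of draws at each correlation. Contrasts picked after seeing the estimates would therefore not solve the problem. They must be few and fixed beforehand.

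**5. Width of a valid contrast.** For a subset against its complement in the parent, taken as independent, the SE in units of the parent's SE is √[1/f + 1/(1 − f)] = 1/√[f(1 − f)]. This is 2.50 at f = 0.2, 2.18 at 0.3, 2.00 at 0.5 and 2.18 at 0.7. Such an interval is at least twice as wide as the one for the whole of (ii).

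**The case against.** The strongest reply is that the between-group aim rests mainly on one hedged sentence. The Objective section asks for SROM against the other drugs among key sub-populations, and the comparator in the Study population aim is likewise the other drugs. Separate emulations answer both. This stands, and it limits the point to statements that rank groups.

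A second reply is that an analysis plan not shown may hold the contrasts. That is possible. But the article states the purpose and then sets out its estimands in detail, and those estimands do not serve that purpose.

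Some stronger readings are tempting but not supported:
- **That overlap would manufacture false differences.** Step 3 shows the opposite for nested groups: ignoring the overlap is conservative for the difference.
- **That the chance of discordant results measures the problem.** With 80% power in each of two independent groups, one interval excludes no effect and the other does not in 2 × 0.8 × 0.2 = 32% of cases. The power and independence are assumed, and the protocol adopts no significance rule; it speaks of compatibility intervals. The figure is an illustration only.
- **That the forest plot is the ranking tool.** The text says "Relevant findings from each analytical approach will be presented in a forest plot", in the section on subgroup and sensitivity analyses. It is organised by analytical approach, and nothing says it will be used to compare the ten sub-populations.
- **That all ten overlap and can be compared with each other.** (i) is disjoint from (iii) to (viii) at episode level, and (ix) and (x) answer a different question.

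**Conclusion.** The point holds in a limited form. Followed as written, the plan yields 68 within-population estimates for the primary outcomes and no between-population quantity, so it cannot support a statement that one group benefits more from SROM than another. The within-population estimates are unaffected.

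The 1.22 to 2.38 range depends on assumed event shares of 20% to 70% and on variance inversely proportional to events. The spread figures depend on assumed equal standard errors and correlations. The conclusion itself depends on neither: it follows from setting the Study design sentence beside the estimands in the analysis sections. A reader might infer that the study's main conclusions are at risk, but the Objective is within-population and is answered by the planned estimates.

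**What to change.** For the initiator and per-protocol analyses of (i) to (viii) only:

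- In each of the 500 bootstrap samples, resample persons once from the full cohort, apply all the sub-population definitions to that sample, and recompute every risk difference. This carries the covariance from shared people.
- Pre-specify a small set of contrasts and report them with intervals. An example is incident (i) versus prevalent (ii), and each of (iii) to (viii) versus its complement within (ii). That is 1 + 6 = 7 per comparator and outcome, or 7 × 2 × 2 = 28 for the primary outcomes in each analysis, against 112 possible pairs.
- Keep (ix) and (x) out, because a switch-versus-stay effect cannot be subtracted from an initiation effect or from the dosing-benchmark effect in (i) to (viii).
- Base any statement on who benefits most on these contrasts alone.

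If the authors prefer not to add contrasts, they should reword the Study design sentence so that it promises descriptive estimates within each sub-population.

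The cost is mainly bookkeeping on bootstrap samples already planned, and the Study status section says no analyses have yet been run. The drawback is precision: the intervals will be wide (step 5), and many contrasts may be inconclusive.
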